## Abstract

*Background*. Physical inactivity is currently seen as one of the biggest global public health issue. Remote physical activity (PA) promotion programs are expected to be effective if they are individually tailored and include behavior change techniques, personal coaching, and regular prompting. However, it is still not fully understood which intervention components are most effective. This paper describes the rationale and design of a study on an individually tailored remote PA promotion program comparing the efficacy of coaching and prompting with a single written advice. *Methods*. In total, 288 adults (age 20 to 65 years) were randomly assigned to three different intervention arms of a 6-month-long PA promotion program. A minimal intervention group received a single written PA recommendation. The two remaining groups either received telephone coaching sessions (*n* = 12 calls) with or without additional short message service (SMS) prompting (*n* = 48 SMSs for each participant). Data assessment took place at baseline, at the end of the intervention, and after a six-month follow-up-period. The primary outcome of the study was self-reported PA. Objectively assessed PA, psychosocial determinants of PA, well-being, body mass index (BMI), and adherence were assessed as secondary outcomes. *Conclusion*. Findings of this three-arm study will provide insight into the short and long-term effects of coaching and prompting for PA promotion.

## 1. Introduction

Physical inactivity is associated with various non-communicable diseases and rising health care costs. As an independent risk factor for cardiovascular disease, physical inactivity accounts for 9% of premature deaths globally [1]. Adults should engage in at least 150 minutes of moderate or 75 minutes of vigorous physical activity (PA) per week [2]. Based on self-reports, approximately 30% of the adult population worldwide as well as in Switzerland do not reach these minimal recommendations [3,4]. Physically inactive lifestyles have been linked to technological developments, mechanization, an increased use of motorized transport, and an increase in sedentary leisure-time activities [4].

The lack of time and motivation represent the main self-reported barriers for leisure time PA in working-aged adults [3,5]. To achieve PA-related behavior changes, adults need support to overcome personal barriers.

Environmental approaches, interventions in social settings (e.g., the workplace), and personal interventions that focus on motivational aspects have been proven to be effective in promoting PA [6]. On an individual level, multicomponent strategies are used to encourage participants to incorporate regular PA in their daily lives. Individually tailored interventions (which consider demographic characteristics and the current behavior) based on empirically validated theories are considered most effective [7]. 

During recent years, an increasing interest has been observed in interventions delivered without a face-to-face interaction. Mobile phone or web-based communication modes are commonly available and enable reach to a wide population. [8]. Compared to face-to-face interventions, remotely delivered programs are considered more cost-effective [9]. An additional benefit is the reduction of time, transportation, and personal contact barriers (i.e., fear of prejudice) [10]. Within remote interventions, telephone contact to provide feedback or to facilitate behavior changes were most effective for promoting self-reported PA [8]. The personal communication enables a further individualization of intervention content and the use of health-coaching techniques. According to Olsen [11], health-coaching refers to a goal-oriented, client-centered, and health-focused interactive partnership between the coach and the participant that is based on a process of enlightenment and empowerment. Combined with other modalities (e.g., print), telephone delivery has shown similar effects to face-to-face interventions [12]. Hence, telephone-based coaching lasting 6–12 months that includes 12 or more calls has been proven effective [13]. The potential to disseminate individually tailored telephone coaching has recently been demonstrated in a population-based study in Australia. After a six-month period with 10 coaching sessions, 1440 participants reported significant improvements in PA levels and body weight [14]. 

Web-based behavior change interventions include the use of (self-navigated) educational information, computer-tailored feedback, goal-setting and self-monitoring applications, and/or access to a counsellor via e-mail or through chat rooms [15]. An existing meta-analysis indicates positive changes in PA levels [16]; however, effect sizes are small. Depending on the level of interactivity, web-based interventions suffer from low engagement and high retention that are associated with decreased effectiveness [16]. 

Periodic prompts represent another remote communication strategy for PA promotion [17]. Periodic prompts are messages sent multiple times without a user-initiated request. They are often delivered as short message services (SMSs) by phone. These intervention have the advantage that 90% of obtained SMS are read within minutes once received [18]. Messages are used as a reminder, to provide feedback, or to share information on strategies to facilitate behavior change [17]. A previous meta-analysis showed a small-to-moderate positive effect of SMS prompting on preventive health behaviors [19]. Thereby messages sent at varying times though out the day and the week seem to be more effective, as they prevent habituation and communicate more “social presence” [20].

Behavior change techniques (BCTs) constitute the “active ingredients” of PA interventions. Independent of their delivery mode and context, BCTs can be categorized according to the V1 Taxonomy developed by Michie et al. [21]. Previous meta-analyses pointed out the effectiveness of certain BCTs to change PA behavior [22,23,24]. In particular, *self-monitoring of behavior* has been associated with intervention effectiveness [24]. Self-monitoring requires the recording of frequency, intensity, or type of PA and makes individuals regularly aware of their current behavior [25]. Existing meta-analyses and reviews [22,23,24,26,27,28,29,30,31] further underline the importance of *goal setting* concerning the behavior and the outcome of the behavior. They additionally emphasize the use of *action planning*, *social support*, *problem solving*, *feedback on performance*, *review of behavior goals*, *instruction on how to perform the behavior*, and *information about health consequences*. Furthermore, a recent meta-analysis by Samdal et al. [32] showed the importance of an autonomy-supportive and person-centered communication mode.

Increases in PA are accompanied by improvements in overall well-being [33] and changes in psychological variables which moderate PA participation (e.g., self-efficacy) [31]. Only few studies examined the effects of PA promotion after a follow-up period without intervention and thus data on long-term outcomes are scarce [8,34]. Additionally, PA levels are usually assessed via questionnaires (e.g., 7-Day Physical Activity Recall [35], International Physical Activity Questionnaire [36]) which are effected by recall and social desirability bias. To date, objective measures (e.g., accelerometer, pedometer) have rarely been used to examine the impact of interventions to promote PA [37].

In summary, there is clear evidence for short-term behavior changes through remote delivery of BCTs. However, it remains unclear which intervention components are most effective and can be translated into practice. In order to gain a better understanding of which specific elements of an intervention result in behavior change, studies with multiple intervention arms and different combinations of intervention components are needed [38]. Furthermore, the maintenance of PA-related behavior change needs to be evaluated across longer periods of time.

Aim of the Study

The main goal of the “Movingcall” study is to evaluate a remote individually tailored PA promotion program based on individually assigned BCTs. More specifically, the following three research questions are addressed: First, what is the short-term effect of remote telephone coaching with and without SMS prompting on self-reported and objectively assessed PA levels in inactive adults compared to a control condition (written information about recommended levels of PA; minimal intervention)? Second, what is the long-term effect (six-month follow-up without contact with participants) of the intervention compared to a control condition? Third, how does the intervention impact on psychological determinants which are involved in the regulation of exercise behavior, and do these determinants mediate the effect of the intervention on PA behavior?

## 2. Materials and Methods 

### 2.1. Study Design

Movingcall is conceptualized as a three-arm randomized controlled trial (Figure 1). The three study arms differ in terms of the delivery mode of the intervention: A “control group” received a single written recommendation at the beginning of the intervention (minimal intervention). A “coaching group” received 12 biweekly telephone coaching sessions. A “coaching and SMS group”, similarly received 12 biweekly telephone coaching sessions which were extended by two SMS messages per week. Data assessment took place at baseline, at the end of the six-month intervention, and after a six-month follow-up period without contact with the participants. The study was conducted at the Department of Sport, Exercise, and Health at the University of Basel, Switzerland.

### 2.2. Recruitment and Sample Size 

Participants were recruited through newspaper advertisements, e-mail newsletters, advertisements provided by local and cantonal administration offices, companies’ communications to employees, and flyers in pharmacies, medical practices, and physiotherapy clinics, as well as by word-of-mouth publicity. Individuals who were interested in participating contacted the study team by e-mail or by phone. Eligible individuals were provided with a written informed consent before participating in the study.

Based on previous studies on remote PA promotion and the comparison of SMS prompts with alternative interventions [8,20] a small effect (d = 0.21) on self-reported PA was expected. Based on this expectation, a sample size calculation for an analysis of covariance (ANCOVA) including baseline PA as a covariate was computed [39]. In order to achieve a power of at least 80% (1-β error probability) and a significance level of 5%, a total of 242 participants were required. A subsequent total sample size of approximately 284 participants was needed after adjusting for an expected dropout rate of 15–20%.

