### 2.4. Group Allocation

A computer-based minimization procedure [42] stratified by age and sex was used to assign participants randomly to one of the three study arms. The randomization was conducted by a member of the research team, who was not involved in the intervention. In order to simplify the allocation of participants within the study team, randomization occurred prior to baseline data collection. Neither the study team nor the participant knew the group allocation prior to the start of the intervention.

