## 3. Discussion

The present paper describes the rationale, design, and content of a randomized controlled trial on remote PA promotion. The evaluation of the three study arms will enable conclusions on effects of coaching and prompting. Telephone coaching [12] based on suitable BCTs [24] as well as SMS prompting [17] has been proven effective to induce PA-related behavior changes. However, so far only few studies compared multiple intervention concepts to elicit, which concept should be translated into practice. Van Wier et al. [85] concluded that lifestyle counselling by phone as well as by e-mail is an effective tool to reduce body weight in comparison to a control condition. Regarding PA behavior changes, only telephone coaching showed significant improvements compared to the control group. Another study by Marcus et al. [86] and one by van Keulen et al. [87] detected no difference in PA levels comparing tailored print to telephone communication for PA promotion. To our knowledge, text messages in combination with telephone counselling sessions have only been conducted in weight loss and disease management studies [88] and have proven effective. Further studies, using multiple intervention arms to compare short- and long-term efficacy of specific intervention concepts are required [38]. Thereby, the provision of a detailed description of intervention contents will help identify evidence-based practice [12].

The present study will expand previous research and contribute to an increased understanding of remote intervention components for PA promotion in working aged adults. We hypothesize that coaching combined with prompting results in a higher and more sustainable increase in PA than coaching alone. We further hypothesize that both coaching groups outperform the minimal intervention group. The analysis of psychosocial determinants of PA will contribute to the theoretical explanation of PA behavior change. The effect of BCT based coaching on specific psychosocial determinants can be explored. Thereby, the precise documentation of applied BCTs will be valuable to further specify the content of the coaching. The three time points of measurements will further allow conclusions on psychosocial determinants relevant for maintenance of PA levels. Finally, the analysis of participants’ engagement with the program as well as their feedback will enable to analyze the feasibility of remote PA promotion in Switzerland.

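### The stated 242 participants do not give 80% power for d = 0.21 in this three-arm trial unless baseline and follow-up activity correlate at about 0.81 to 0.90, and no correlation is stated

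*Protocol article*

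**What the plan says.** Section 2.2 (Recruitment and Sample Size) states that "a small effect (d = 0.21) on self-reported PA was expected", citing earlier work on remote activity promotion and on SMS prompts against alternatives. It then says that "a sample size calculation for an analysis of covariance (ANCOVA) including baseline PA as a covariate was computed". For power of at least 80% at the 5% level, "a total of 242 participants were required". The allowance for loss follows: "A subsequent total sample size of approximately 284 participants was needed after adjusting for an expected dropout rate of 15–20" percent. The section does not say which comparison d refers to, whether the test is one- or two-sided, or what correlation between baseline and follow-up was assumed.

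Section 2.4 (Group Allocation) describes a procedure to "assign participants randomly to one of the three study arms". The Discussion frames the hypotheses as comparisons between arms: "We hypothesize that coaching combined with prompting results in a higher and more sustainable increase in PA than coaching alone", and both coaching arms are expected to do better than the minimal intervention. The Abstract reports 288 randomised, so recruitment is complete.

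**The concern.** A standardised difference of 0.21 is small, and small differences normally need several hundred participants per arm. A total of 242 over three arms leaves about 81 per arm. Baseline adjustment reduces the residual variance by the factor 1 − r², where r is the correlation between baseline and follow-up, so the adjustment would have to do nearly all the work.

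The SMS question is the most exposed. It compares two active arms, and SMS comparisons are part of the stated basis for d = 0.21. If power for that contrast is well below 80%, a non-significant result says little about whether prompting adds anything, yet a reader who relies on section 2.2 would give it more weight.

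**Working it through.** **Inputs from the article:** d = 0.21, ANCOVA with baseline as the only named covariate, power 80%, level 5%, 242 analysed, three arms. **Assumed:** 1:1:1 allocation (242/3 = 80.67 per arm), a two-sided test, and r from 0 to 0.9, because none is given.

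**1. The dropout step.** 242/0.85 = 284.7, which agrees with the stated figure of about 284. (At 20% loss, 242/0.80 = 302.5.) So 242 is the number to be analysed.

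**2. Size needed for a pairwise contrast.** n per arm = 2(1.96 + 0.8416)²(1 − r²)/d² = 2 × 7.849/0.0441 × (1 − r²) = 356(1 − r²).
- r = 0: 356 per arm, or 1,068 for three arms.
- r = 0.5: 267 per arm, or 801 for three arms.
- For 80.67 per arm, 1 − r² = 80.67/356 = 0.227, so r = 0.88.
- If 242 is read as a two-arm total (121 per arm), 1 − r² = 0.340, so r = 0.81.

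**3. Size needed for the three-arm omnibus test.** Noncentral F with 2 and N − 4 degrees of freedom and noncentrality f²N/(1 − r²). A d of 0.21 between the extreme arms gives f = 0.21/√6 = 0.086 if the middle arm lies at the mean, and f = 0.21 × √2/3 = 0.099 if one arm differs from the other two. The two-group conversion f = d/2 = 0.105 is more generous than either. With r = 0 these need 1,314, 987 and 877 participants. With N = 242, 80% power needs r of about 0.90, 0.87 and 0.85.

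**4. Power with 242 analysed.** Pairwise power = Φ(d/√[(2/n)(1 − r²)] − 1.96). With n = 80.67 and r = 0 this is Φ(0.21/0.1575 − 1.96) = Φ(−0.63) = 27%.

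| r | Pairwise, 81 v 81 | Omnibus, three arms | 242 as two arms of 121 |
|---|---|---|---|
| 0 | 27% | 20–29% | 37% |
| 0.5 | 34% | 26–37% | 47% |
| 0.7 | 46% | 36–52% | 63% |
| 0.8 | 60% | 49–68% | 78% |
| r for 80% | 0.88 | 0.85–0.90 | 0.81 |

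Analysing all 288 randomised without loss (96 per arm) gives pairwise power of 31%, 39% and 53% at r = 0, 0.5 and 0.7.

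**5. Pairwise difference detectable with 80% power.** d = 2.8016 × √(2/80.67) × √(1 − r²) = 0.441 × √(1 − r²), that is 0.44 (r = 0), 0.38 (r = 0.5) and 0.32 (r = 0.7).

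**6. What effect would give 242.** A three-group, one-covariate ANCOVA with no credit for r has 80% power at N = 242 when f = 0.201. For two equal groups that is d = 2f, about 0.40, roughly twice the stated value. The round value f = 0.20 gives 244, and f = 0.21 gives 222.

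**The case against.** The strongest reply is that a journal article condenses the full protocol, and that the correlation, the sidedness and the named contrast may stand there. That is fair as far as it goes: their absence is not itself an error. But supplying them rescues 242 only if the correlation was set at about 0.81 to 0.90. One-sided testing, which is not stated, lowers the requirement only to about 0.84 pairwise, or 0.75 for two arms of 121.

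A second reply is that the mixed model in section 2.8 uses both post-baseline visits. Averaging them, with the same correlation between all visits, multiplies the variance by (1 + r)/2 − r². Pairwise power becomes 47% at r = 0.5 and 74% at r = 0.8, which is better than one visit but still short of 80%.

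A third is that 242 may come from another formula. A repeated-measures interaction calculation with f = 0.10, three arms and three time points gives 242 at r = 0.4; two time points give 244 at r = 0.5. Section 2.2 names an ANCOVA, however, and f = 0.105, which matches d = 0.21, gives 219 and 222. If that route was taken, the method is misdescribed and the text still needs correcting.

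Some stronger readings should be resisted:
- **A single true power of 20–50%.** At r = 0.7 to 0.8 the figures run from 36% to 78% depending on the contrast.
- **The required correlation is not credible.** The article gives no 6- or 12-month correlation for this interview measure, so it supports no judgement either way.
- **242 shows that an omnibus test was planned, or that d was entered as f.** Both are possible, but the alternative route above shows that 242 does not identify its source.
- **The trial can detect only a medium effect.** Detectable values of 0.32 to 0.44 are small to medium.

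**Conclusion.** The power statement in section 2.2 does not follow from its own inputs. For d = 0.21, two-sided 5% and 242 analysed in three equal arms, pairwise power is 27% to 46% for correlations from 0 to 0.7, and 60% at 0.8. The claim of at least 80% holds only at an unstated correlation of about 0.88 pairwise, 0.85–0.90 omnibus, or 0.81 on the two-arm reading. Equal allocation, a two-sided test and the values of r are assumptions. If 0.21 is already on the covariate-adjusted scale, the r = 0 row applies (20–37% across the three readings). The failure to reproduce is firm; its cause and the trial's actual power cannot be settled from the article.

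**What to change.** Reword section 2.2; no change to enrolment, allocation or endpoint is needed. Replace the power statement with what the design delivers, for example: *About 81 analysed per arm gives 80% power for a pairwise d of 0.44, 0.38 or 0.32 at a baseline to follow-up correlation of 0, 0.5 or 0.7; power for d = 0.21 is about 27–46% over that range.* If 242 came from a different effect metric or method, correct the text to say so.

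Add that a non-significant comparison of coaching plus SMS with coaching will be interpreted by the confidence interval of the between-arm difference, and not as evidence of no effect. Section 2.8 already promises confidence intervals, but for effect sizes of pre-post change scores, so the between-arm interval should be named. The cost is a less favourable stated power.

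### The dropout-adjusted total of about 284 matches only the 15% end of the stated 15–20% range; 20% would need 303

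*Protocol article*

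**What the plan says.** Section 2.2 (Recruitment and Sample Size) of the protocol article gives the whole chain in three sentences. The assumption is that "a small effect (d = 0.21) on self-reported PA was expected". The method is that "a sample size calculation for an analysis of covariance (ANCOVA) including baseline PA as a covariate was computed". The target is "a power of at least 80% (1-β error probability) and a significance level of 5"%, for which "a total of 242 participants were required". The article then adds an allowance for loss: "A subsequent total sample size of approximately 284 participants was needed after adjusting for an expected dropout rate of 15–20"%.

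One total is given for a range of rates. The text does not say which rate or which formula produced it.

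The Abstract reports the number actually enrolled: "In total, 288 adults (age 20 to 65 years) were randomly assigned to three different intervention arms". Section 2.6.6 defines dropouts as people lost to the post and follow-up tests, so the allowance concerns missing outcome data and not merely stopping the coaching.

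**The concern.** The required number, the dropout range and the adjusted total stand next to each other, and they do not agree over most of the range. A total said to adjust for 15–20% dropout should leave the required 242 when 20% are lost, or the text should say that it was set at a lower rate.

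What is at stake is the power assurance. The final assessment comes at 12 months, after six months without contact, and readers will compare the observed dropout with Section 2.2 to judge whether the trial kept its power. As written, the section tells them that a loss anywhere up to 20% was allowed for.

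**Working it through.** **Inputs**
- Evaluable number required: 242 (Section 2.2)
- Expected dropout: 15–20% (Section 2.2); the midpoint, 17.5%, is added here for illustration
- Stated adjusted total: about 284 (Section 2.2)
- Number randomised: 288 (Abstract)

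The check takes 242 as given. It does not test whether 242 follows from d = 0.21.

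**Step 1. Reproduce the stated total.** To keep n evaluable after a loss d, randomise N = n/(1 − d). At d = 15%: 242/0.85 = 284.7. This agrees with about 284 to within one participant, so the plan's figure is reproduced at the lower bound.

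**Step 2. Apply the same formula across the range.**

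| Dropout | 242/(1 − d) | Needed | Short with 284 | Short with 288 |
|---|---|---|---|---|
| 15% | 284.7 | 285 | 1 | none |
| 17.5% | 293.3 | 294 | 10 | 6 |
| 20% | 302.5 | 303 | 19 | 15 |

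**Step 3. Find the loss that each total covers**, 1 − 242/N.
- 284: 1 − 242/284 = 14.8%, in effect 15%
- 288: 1 − 242/288 = 16.0%

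**Step 4. Find the number left**, N × (1 − d).

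| Dropout | From 284 | From 288 |
|---|---|---|
| 15% | 241.4 | 244.8 |
| 17.5% | 234.3 | 237.6 |
| 20% | 227.2 | 230.4 |

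**Step 5. Effect on power, under an assumption.** The article gives neither the correlation between baseline and outcome nor the effect size in the form an ANCOVA F test uses, so the power at smaller numbers cannot be computed from the text alone. As a stand-in, take a three-group ANCOVA F test with one covariate at the 5% level (2 and N − 4 degrees of freedom, noncentrality N × f²) and choose f so that power is 80% at N = 242. This gives f ≈ 0.201 and a noncentrality of about 9.76. Holding f fixed:
- 227 left (284 randomised, 20% lost): noncentrality about 9.15, power about 77%
- 230 left (288 randomised, 20% lost): noncentrality about 9.27, power about 78%
- 241 left (284 randomised, 15% lost): power 79.8%, in effect 80%

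**The case against.** The strongest reply is that the article says approximately, and 284 is 242/0.85 = 284.7 cut to a whole number. A reader might set the 14.8% covered against the stated 15% and infer that the total misses the entire range. The documents do not support that. The gap at 15% is 0.6 of a participant (242 − 241.4), which is rounding. This part of the reply stands, and the point is limited to rates above the lower bound. The word cannot also absorb 10 participants at the midpoint or 19 at the upper bound.

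Second, 288 were randomised, not 284, and 288 × 0.85 = 244.8 exceeds 242. This is right, and it moves the limit to about 16%. The range between 16% and 20% stays uncovered.

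Third, the practical loss is small. Section 2.8 plans intention-to-treat linear mixed models, and Section 2.6.6 says that people who stop coaching are still asked to take part in later tests. Someone who misses one assessment can therefore still contribute. That is a fair mitigation, though only a partial one: a person lost to both later tests contributes no outcome after baseline.

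A reader might also notice that 242 × 1.175 = 284.35 and conclude that the authors multiplied by one plus the midpoint rate instead of dividing. The article does not say how 284 was obtained, and 242/0.85 explains it equally well. Nothing here depends on which it was.

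**Conclusion.** The point holds in a limited form. The total of about 284 is right for 15% dropout and is described as adjusting for 15–20%. With 284 the required 242 is protected only at about the lower bound; with the 288 randomised it is protected up to about 16%, one point of a five-point range. Section 2.2 states all the figures involved, so this is a disagreement within the text and not a detail left to a fuller document.

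The head counts follow directly from the article's own numbers. The power figures do not: about 77% and about 78% at 20% dropout rest on an effect size back-solved from 80% power at 242 and on a three-group test, and they should not be read as the plan's own values. On that assumption the cost is 2 to 3 percentage points at the worst rate in the range.

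A reader might go further and infer that the trial ended up underpowered through dropout. The article does not support that, because it reports no observed dropout. What can be said is that the stated assurance does not extend to the upper part of the expected range.

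**What to change.** Reword the last sentence of the sample size paragraph in Section 2.2 along these lines: *242 evaluable participants require 285 randomised at 15% dropout and 303 at 20%; the 288 randomised preserve 242 up to about 16% dropout, and at 20% about 230 remain.* Add the power for 230, computed from the sponsor's own calculation inputs and not from the back-solved value used above.

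No extra enrolment and no change to design or analysis is needed. The cost is one sentence and a slightly less favourable stated figure.
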